### Statistical Analysis

Results will be presented as means with standard deviations for continuous variables and as frequencies and percentages for categorical variables. The *χ*^2^ test or Fisher exact test will be used for categorical data, while the Student’s t-test or Mann-Whitney *U* test will be applied to continuous data. Logistic regression will be conducted for univariate and multivariate analyses. For adjusted analyses, prespecified covariates will include age, sex, body mass index, tumor location, clinical stage, neoadjuvant treatment history, operative approach, anastomotic level, and the interval between index rectal surgery and ileostomy closure. Exploratory subgroup analyses may be performed according to sex, age group, operative approach, and anastomotic level. Because the study is not powered for subgroup comparisons, these analyses will be interpreted cautiously. A *P* value <.05 will be considered statistically significant.

Analyses will be conducted on an intention-to-treat basis, including all randomized participants in their assigned groups, regardless of protocol adherence. A per-protocol analysis will be performed as a sensitivity analysis to assess result robustness. For missing data, multiple imputation methods will be employed, assuming data are missing at random. Sensitivity analyses will evaluate the impact of missing data on primary and secondary outcomes. Statistical analyses will be conducted using SPSS software (version 25; IBM Corp., Armonk, NY, USA).

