### Outcomes

The primary outcome is the LARS score at 3 months after ileostomy closure. The LARS score is a validated patient-reported outcome measure based on 5 items: incontinence for flatus, incontinence for liquid stools, bowel frequency, clustering of stools, and urgency. The total score ranges from 0 to 42, with higher scores indicating more severe bowel dysfunction. Scores are categorized as no LARS (0‐20), minor LARS (21-29), and major LARS (30-42). The questionnaire will be administered in the outpatient clinic at 3 months postoperatively.

The secondary outcomes include (1) postoperative complications within 30 days after ileostomy closure, including ileus, surgical site infection, anastomotic-related complications, readmission, and reoperation; (2) severity of postoperative complications, graded according to the Clavien-Dindo classification; (3) bowel recovery parameters, including time to first flatus, time to first stool passage, and tolerance of oral intake; (4) stool habits, including stool frequency and stool form assessed using patient records and the Bristol Stool Chart; (5) laboratory findings obtained during follow-up; and (6) length of postoperative hospital stay.

Patients will enter an open follow-up phase for up to 5 years for routine postoperative surveillance, monitoring oncologic outcomes and late complications through periodic clinical visits and imaging studies per institutional guidelines.

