### Sample Size Calculation

The sample size calculation was based on the primary outcome, the LARS score at 3 months after ileostomy closure. Based on a previous study [21], we considered a 3-point between-group difference in LARS score to be clinically relevant. For the sample size estimation, the standard deviation was conservatively assumed to be 5 points. Using a 2-sided significance level of .05 and 80% power, 45 participants were required per group. Allowing a 10% dropout rate, the final target sample size was set at 100 participants (50 per group).

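### The only regression model named is logistic, so the plan states no suitable adjusted model for its primary endpoint, a 0 to 42 score powered on a mean difference (should-fix)

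*Protocol article*

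**What the plan says.** All references are to the protocol article.

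- **Outcomes:** "The primary outcome is the LARS score at 3 months after ileostomy closure". The scale is numeric: "The total score ranges from 0 to 42, with higher scores indicating more severe bowel dysfunction". Bands are given for interpretation, with none at 0 to 20, then "minor LARS (21-29), and major LARS (30-42"). No band is declared an endpoint or a cut-point for a model.
- **Sample Size Calculation:** "we considered a 3-point between-group difference in LARS score to be clinically relevant", and "the standard deviation was conservatively assumed to be 5 points". With two-sided alpha .05 and 80% power, this gives 45 per group, raised to 50 per group for 10% dropout.
- **Statistical Analysis:** for unadjusted comparisons, Student's t-test or the Mann-Whitney U "test will be applied to continuous data". For regression, "Logistic regression will be conducted for univariate and multivariate analyses". The next sentence lists the covariates for adjusted analyses: age, sex, body mass index, tumour location, clinical stage, neoadjuvant treatment history, operative approach, anastomotic level, and the interval from rectal surgery to closure. No linear model, ANCOVA or ordinal model is mentioned.

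**The concern.** Outcomes and Sample Size Calculation treat the endpoint as continuous and the effect as a difference in means. The regression sentence commits to a model family that, in its ordinary form, needs a binary response. So the covariate list has no stated model through which it can act on the endpoint the trial is powered on.

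This is more than detail left to an analysis plan. The article does choose a model family and a covariate list, and that family does not suit the primary endpoint.

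Two things are at stake. Followed literally for the LARS score, the text leads to a cut-point chosen later, an odds ratio in place of a mean difference, and less power. If the sentence is instead ignored for the LARS score, the adjusted model is chosen after data exist, and the value of prespecifying the covariates is partly lost.

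**Working it through.** **Inputs from the article:** difference 3, SD 5, two-sided alpha 0.05, 45 per group, cuts at 21 and 30. **Assumptions:** normal scores with a 3-point shift, and a range of control means, because the article gives none.

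**1. Reproduce the planned size.** Normal approximation: n = 2(1.960 + 0.842)² × 5²/3² = 43.6, so 44 per group. The exact noncentral-t calculation gives power 0.795 at 44 and 0.804 at 45, so 45 per group is right. Dropout: 45/0.90 = 50. The unadjusted t-test therefore has the stated power of about 80%.

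**2. Power if the score were dichotomised.** With cut c (29.5 for major LARS, 20.5 for any LARS) and control mean m:

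p₁ = 1 − Φ((c − m)/5), p₂ = 1 − Φ((c − m + 3)/5)

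power = Φ[(|p₁ − p₂| − 1.96·SE₀)/SE₁], where SE₀ uses the pooled and SE₁ the separate variances.

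The best case is a cut midway between the arm means (m = 31 for the cut at 30):

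- p₁ = 0.618, p₂ = 0.382, difference 0.236.
- SE₀ = √(0.25 × 2/45) = 0.1054. SE₁ = √(2 × 0.2361/45) = 0.1024.
- Power = Φ((0.2358 − 0.2066)/0.1024) = Φ(0.285) = 0.61.

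| Assumed control mean | Power, cut at 30 | n per group for 80%, cut at 30 | Power, cut at 21 |
|---|---|---|---|
| 22 | 0.21 | 265 | 0.61 |
| 25 | 0.39 | 125 | 0.55 |
| 28 | 0.55 | 81 | 0.39 |
| 31 | 0.61 | 70 | 0.21 |
| 34 | 0.55 | 81 | 0.10 |

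The loss is thus at least about 19 percentage points (0.804 against 0.612). At best 70 per group would be needed in place of 45, or 70/45 = 1.56 times as many. These figures are for the arm comparison alone. Prognostic covariates would add some power to either model, so the like-for-like contrast is 61% with 80%.

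**3. Few events.** At control mean 25 with the cut at 30, the expected number with major LARS is 45 × (0.184 + 0.067) = 11.3 of 90. Treatment plus nine covariates is at least ten coefficients, or about one event per coefficient.

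**4. Ordinal alternative.** A rank test on the three bands, simulated (2,000 runs per setting, control means 22 to 31), had power of about 0.65 to 0.70. That is better than one cut but still below 0.80.

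**5. Linear model on the full score.** If covariates explain a share R² of the variance, the residual SD is 5√(1 − R²).

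- R² = 0.1: SD 4.74, exact power 0.84.
- R² = 0.2: SD 4.47, exact power 0.88.

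Both R² values are assumed; the article gives none.

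**The case against.** The strongest reply is that the primary comparison is sound. The outcome, the sample size and the t-test agree with one another, and an unadjusted comparison under 1:1 randomisation is valid. That stands in full.

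It can also be said that the regression sentence sits in a general paragraph covering all outcomes. Ileus, surgical site infection, readmission and reoperation are binary, and logistic regression suits them. The covariate sentence does not say that every adjusted analysis is logistic. This also stands. It narrows the point but does not remove it: on that reading, the article still states no model for adjusting the primary endpoint.

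A reader might go further and infer any of the following, which the article does not support:

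- **That the primary analysis will dichotomise the score and so has only 39% to 61% power.** The article nowhere plans a cut. Those figures describe a hypothetical adjusted analysis at the cut of 30 and assumed control means of 25 to 32.
- **That logistic regression cannot be used without dichotomising.** This is true of the binary form only. An ordinal model is possible, though not named.
- **That leaving open the t-test or Mann-Whitney inflates type I error to about 6%.** That simulated figure requires taking the smaller of the two P values, which the plan does not say it will do.

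Finally, the gain from ANCOVA may be modest. The Postoperative Management and Follow-Up section describes the LARS questionnaire only at 3 months, and no baseline score is among the covariates. This is fair, and is why the gains above are illustrations only.

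**Conclusion.** The point holds in limited form: the article names one regression model, and it does not suit the endpoint on which the trial is powered, so the prespecified adjustment has no stated model for that endpoint.

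The primary unadjusted comparison, the sample size and its 80% power are intact. The consequence falls on the adjusted analysis. If that took the form of binary logistic regression on a dichotomised score, power would be at most about 61% under the plan's own difference and SD, and lower when the cut lies away from the midpoint between the arm means. This rests on normal scores and on control means that the article does not give, but the ceiling does not depend on knowing the control mean. The estimate would also change from a mean difference to an odds ratio.

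This should be fixed, but it does not threaten the validity of the trial.

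**What to change.** Amend the Statistical Analysis section as follows:

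1. State that the adjusted analysis of the 3-month LARS score is a linear regression (ANCOVA) on arm and the prespecified covariates. Report the adjusted mean difference with its 95% CI, pooled over the multiple imputations already planned.
2. Name one primary analysis, either the t-test or this linear model, with Mann-Whitney as supportive. Both candidates estimate the mean difference on which the trial was sized. Which of the two is primary is a design choice.
3. Restrict logistic regression to binary outcomes, such as complications. If major LARS is analysed this way, state the cut (30 or more), label it secondary, and keep the covariates few enough for the expected events.

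The cost is a few sentences. The covariates are already prespecified, SPSS fits the model, and no patients or visits are added. The article reports that no participant has been randomised, so the change can be made now with no suspicion that data drove it.

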### Study Participants

Patients with rectal cancer who have undergone low anterior resection and a diverting ileostomy following chemoradiation and are scheduled for ileostomy closure will be enrolled. The investigator will provide detailed information about the study’s objectives, interventions, potential benefits, risks, and participant rights, allowing sufficient time for consideration. Patients will receive an informed consent form and may voluntarily sign it. Consent will also be obtained for reviewing medical records and collecting blood samples for recurrence assessment. Declining participation will not affect treatment, and patients may withdraw from the study at any time.

Inclusion criteria were as follows: (1) age 18‐80 years; (2) histologically confirmed rectal adenocarcinoma; (3) clinical stage II or III disease; (4) completion of neoadjuvant chemoradiotherapy; (5) prior laparoscopic or robotic low anterior resection with total mesorectal excision and creation of a diverting ileostomy; and (6) planned elective ileostomy closure after confirmation of anastomotic integrity.

Exclusion criteria were as follows: (1) suspected or confirmed inflammatory bowel disease; (2) evidence of anastomotic leakage, stricture, or distal obstruction precluding ileostomy closure; (3) medical contraindication to surgery; (4) severe immune-compromised status or uncontrolled systemic illness; and (5) inability or unwillingness to provide informed consent.

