### Probiotics Administration

The patients will receive a 14-French Foley catheter, normal saline, and probiotics (Lacidofil®) containing *Lactobacillus rhamnosus* R0011 and *Lactobacillus acidophilus* R0052 bacterial culture (2×109 colony-forming units) in an outpatient setting. This formulation was considered appropriate for the present trial because Lactobacillus-based probiotics have been investigated in colorectal and other gastrointestinal settings as microbiota-modulating interventions, although evidence remains inconclusive regarding their effect on postoperative bowel function and LARS [20]. The probiotic dose was selected to ensure a practical and standardized daily regimen for outpatient administration while remaining aligned with the commercially available formulation and with doses that have been evaluated in prior studies using the same product or closely related probiotic preparations [21]. The intervention group will receive 250 mL of normal saline with 4 g of Lacidofil® administered via the distal limb of the ileostomy once daily for 2 weeks prior to ileostomy closure. The control group will receive 250 mL of normal saline without probiotics using the same method. The 250 mL of normal saline will be infused over 10‐15 minutes via a 14-French Foley catheter with the patient in a supine position. Adherence will be monitored through daily patient diaries and weekly outpatient visits. Patients will record abdominal symptoms, including pain, nausea, vomiting, diarrhea, and gas and stool passage during the 2-week period before ileostomy closure.

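### The adjustment list for the supporting analyses includes a covariate that eligibility makes constant on a yes/no reading and an interval completed only after randomization, and it is too long for the one regression named, which is logistic

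*Protocol article*

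**What the plan says.** The Statistical Analysis section names one regression method: "Logistic regression will be conducted for univariate and multivariate analyses". It then fixes the adjustment set: five patient and tumor characteristics (sex, age, BMI, clinical stage and tumor location) and "neoadjuvant treatment history, operative approach, anastomotic level, and the interval between index rectal surgery and ileostomy closure". That is nine covariates. The section does not say which outcome the logistic model is for, and it does not call the adjusted analysis primary. Continuous data are compared by t-test or Mann-Whitney test.

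Study Participants lists "completion of neoadjuvant chemoradiotherapy" as an inclusion criterion, and the same section says that patients who "are scheduled for ileostomy closure will be enrolled". Under Probiotics Administration the allocated instillation is "administered via the distal limb of the ileostomy once daily for 2 weeks prior to ileostomy closure", with saline alone given by the same method in the control group. Under Outcomes, the primary outcome is the LARS score (0 to 42) at 3 months after closure.

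**The concern.** Three features of the list deserve attention.

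- **A constant.** If neoadjuvant treatment history means received or not received, eligibility gives everyone the same value.
- **A variable completed after randomization.** The closure date comes at the end of the allocated two weeks. If symptoms during those weeks led to deferral, and did so differently by arm, the covariate would carry part of the treatment's effect. Adjusting for it could then distort the adjusted comparison.
- **Length.** Arm plus nine covariates is at least ten coefficients, and more if any covariate has several categories. In logistic regression the number of events limits how many coefficients can be supported, and a trial of 100 has few events.

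At stake is the credibility of the adjusted odds ratios: an estimate that is too large on average, has a wider spread, and includes one covariate not fixed at randomization.

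**Working it through.** **The plan's own figure.** From Sample Size Calculation: difference 3, SD 5, two-sided alpha .05, power 80%. The normal approximation gives n = 2 × (1.960 + 0.842)² × 5² / 3² = 43.6, so 44 per group. By the noncentral t, power is 79.5% at 44 and 80.4% at 45, so 45 reproduces. With 10% dropout, 45 / 0.9 = 50 per group. That leaves 90 evaluable, or 100 if multiple imputation restores everyone. The calculation is for an unadjusted comparison of means.

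**Constant covariate.** A design matrix of intercept, arm and a constant has rank 2 of 3. The constant cannot be estimated and is dropped, and the arm coefficient does not change. The number of estimable coefficients is therefore 9 (arm plus eight) on the yes/no reading and 10 otherwise.

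**Order of events.** Enrollment, envelope opened, two weeks of allocated instillation, closure. The interval from index surgery to closure thus includes at least two weeks after randomization. The part up to randomization is a true baseline quantity.

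**Events per coefficient, logistic model.** The article gives no event rate, so 10% to 50% is assumed.

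| Assumed rate, N = 90 | Events | Per coefficient (10) | Per coefficient (9) |
|---|---|---|---|
| 10% | 9 | 0.9 | 1.0 |
| 30% | 27 | 2.7 | 3.0 |
| 50% | 45 | 4.5 | 5.0 |

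If the outcome were major LARS (30 or more, cut at 29.5), the plan's SD and difference allow a check, with the control mean assumed.

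- Control mean 27, treated 24: 45 × (0.309 + 0.136) = 20 events.
- Control mean 31, treated 28: 45 × (0.618 + 0.382) = 45 events, the maximum.
- Control mean 35, treated 32: 70 events, so the smaller class is 20.

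The smaller class is thus 20 to 45, or 2.0 (20/10) to 5.0 (45/9) per coefficient.

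**Simulation, logistic.** N = 90, arm plus eight independent covariates unrelated to outcome, true log OR −0.693 (OR 0.5), 1,500 data sets per setting.

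| Control rate | Expected events | Adjusted mean (SD) | Unadjusted mean (SD) | Adjusted mean / true | SD ratio |
|---|---|---|---|---|---|
| 15% | 45 × (0.150 + 0.081) = 10.4 | −0.832 (0.974) | −0.697 (0.742) | 1.20 | 1.31 |
| 30% | 45 × (0.300 + 0.176) = 21.4 | −0.813 (0.647) | −0.725 (0.540) | 1.17 | 1.20 |
| 45% | 45 × (0.450 + 0.290) = 33.3 | −0.806 (0.569) | −0.723 (0.483) | 1.16 | 1.18 |

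At 15%, 110 of the 1,500 fits failed and are left out of the means. With no true effect the adjusted estimates centred on zero (−0.013 to −0.004), so the inflation concerns the size of a real effect.

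**Linear model of the LARS score.** If the covariates explain nothing, the standard error grows by about √[(N − 3)/(N − p − 2)], where p counts arm and covariates. For N = 90 and p = 10 this is √(87/78) = 1.056. In 3,000 simulated data sets with arm plus eight such covariates, the mean estimate was −2.98 for a true −3, type I error was 4.7%, and power was 75% against 79% unadjusted.

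**The case against.** The strongest reply is that nothing here touches the main result. The t-test or Mann-Whitney comparison stands apart from the covariate list, and the sample size rests on that unadjusted comparison. This is correct. A reader might infer that the randomized comparison itself is broken, but the article does not make the adjusted analysis primary.

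A reader might also infer that the interval removes never-closed patients from the intention-to-treat set. That does not follow: such a patient also has no LARS score at 3 months after closure, so the endpoint definition already affects them, and multiple imputation is planned.

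Bias from the interval requires the probiotic itself to shift closure dates. Closure is already scheduled at enrollment, both arms receive the same saline instillation, most of the interval probably precedes randomization, and surgeons are blinded until after anesthesia begins. The bias is possible but probably small.

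Neoadjuvant treatment history is not defined and could mean a detail that varies. Even on the yes/no reading, a constant is redundant and does not bias the arm estimate.

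The claim that the list is too long for about 90 patients whatever the model also fails, because a linear model copes well. Covariates that explain nothing are its worst case, and prognostic ones would improve its precision. That tumor location and anastomotic level largely duplicate each other is not stated in the article, and correlation between two covariates would not by itself destabilize the arm coefficient.

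What stands is that the list is called prespecified, the only model named is logistic, and two entries need correction or definition.

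**Conclusion.** The point holds for the supporting adjusted analyses only. One covariate carries no information on its plain yes/no reading. One is completed after randomization, with a possible but probably small bias. The logistic model has at most about 4.5 to 5 events per coefficient at N = 90, and about 1 for a complication at an assumed 10% rate. Under assumed control rates of 15% to 45%, an odds ratio of 0.5 and uninformative independent covariates, the adjusted log odds ratio is about 16% to 20% too large and its SD about 18% to 31% larger than unadjusted. These sizes depend on event rates that the article does not give and on an outcome that it does not name for the logistic model. The primary unadjusted comparison is unaffected.

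**What to change.** 1. Drop neoadjuvant treatment history, or replace it with a named neoadjuvant detail that varies among eligible patients.
2. Measure the interval from index rectal surgery to randomization.
3. State that the adjusted analysis of the LARS score is a linear model with baseline covariates.
4. For any logistic model of a binary outcome, name the outcome and use a short prespecified set of baseline covariates, with the longer list as a sensitivity analysis. Which covariates to keep is the investigators' choice.

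The cost is analysis wording only. The article reports that no participant had been enrolled at submission, so the change can be made before any data exist.

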### Data Collection and Monitoring

Data will be collected using a standardized case report form and entered into a Microsoft Access database. Collected data will include demographic characteristics, baseline clinical variables, perioperative findings, intervention adherence, patient-reported bowel symptoms, dietary intake logs, Bristol Stool Chart records, laboratory results, postoperative complications, and follow-up outcomes including the LARS questionnaire. Data accuracy will be monitored through double data entry and weekly audits.

Participant retention will be promoted through reminder calls and flexible outpatient visit scheduling. Regardless of findings, results will be submitted for publication in a peer-reviewed journal. A data monitoring committee is not required, as probiotics are classified as low-risk interventions per International Council for Harmonisation (ICH) Good Clinical Practice (GCP) guidelines and prior studies [12,15]. No interim analyses are planned, and the study will conclude upon data collection completion unless unexpected adverse events prompt a halt and review.

